**Methods/design:**

Using a hybrid type 1 clinical effectiveness-implementation design, we will collaborate with CMHCs and juvenile justice in two rural Indiana counties. Guided by the EPIS (exploration, preparation, implementation, sustainability) framework, we will measure factors that affect implementation of substance use screening in juvenile justice and implementation of substance use interventions in CMHCs utilizing self-reports and qualitative interviews with juvenile justice and CMHC staff pre- and post-implementation. YIJJ with mild/moderate substance use will receive a brief interventions and YIJJ with severe substance use will receive ENCOMPASS. We will measure the effectiveness of a brief and comprehensive intervention by assessing changes in substance use across treatment. We anticipate recruiting 160 YIJJ and their caregivers into the study. We will assess intervention outcomes utilizing baseline, 3-, and 6-month assessments.

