##### Measuring treatment response

Following completion of the first round of brief interventions (three sessions of Teen Intervene), we will measure youth’s response to treatment. Treatment response will be measured utilizing the Brief Situational Confidence Questionnaire (BSCQ), an eight item self-report measure of one’s level of confidence in resisting urges to use substances in eight situations: unpleasant emotions, physical discomfort, pleasant emotions, testing of control, urges and temptations, conflict with others, social pressures, and pleasant times with others [42]. Individuals rate their confidence in abstaining from substance use in each of the situations on a 0% (*not at all confident*) to 100% (*completely confident*), with higher scores denoting greater confidence in abstaining from substance use. Treatment response will be determined utilizing a cut-off overall mean score of 70% on the BSCQ (i.e., average of 70% confidence in abstaining from using substance use across all eight scenarios), based on results from previous studies utilizing the BSCQ as a measure of symptom improvement [43]. The cutoff of 70% has two advantages: it is the average treatment response expected for this intervention, and it yields (approximately, if the distribution is symmetric) an anticipated equal sample-size split for responders and non-responders for the second randomization. Those with a post-intervention score of 70% or higher will be considered “treatment responders” and those whose BSCQ post-intervention score is lower than 70% will be considered “treatment non-responders.” Those youth who are considered “responders” will be told that they have successfully completed the intervention; they will complete additional post-treatment measures at 3 and 6 month follow-up. Non-responders will continue to the second randomization.

Following completion of treatment response measures using the BSCQ, those who are identified as “non-responders” (i.e., mean post-test BSCQ score lower than 70) will complete a second round of brief interventions. If youth continue to not respond, clinicians will make recommendations and referrals as appropriate. Following completion of the second round of brief intervention, treatment response will be measured again using the BSCQ and participants will complete 3- and 6- month follow-up (see Fig. 2).

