### Data analysis

#### Measurement of intervention effectiveness and treatment response

##### Preliminary analyses

Preliminary analyses will be used to compare the primary treatment response outcome (confidence of abstaining measured by the BSCQ) and substance use outcome across the responders and non-responders of the brief intervention and ENCOMPASS at baseline, 3 months, and 6 months. A separate model will be utilized to measure effectiveness among those assigned to ENCOMPASS. Substance use will be calculated as number of days in the past month of using alcohol, marijuana, and other substances (range 0–90). These outcomes will be compared between groups with longitudinal generalized linear models (GLM) using the GENMOD procedure with a linear link and normal error distribution. The BSCQ and substance use outcome will be analyzed in separate models. The baseline measure of BSCQ or substance use days will be adjusted as covariates and the repeated measurements of each outcome at 3 months and 6 months will be analyzed simultaneously in the model.

The GLMs are easily fit for non-Gaussian distributions by specifying appropriate link functions and error distributions. If substance use days exhibit sparse counts or large frequency of zeros, we will consider using logistic, Poisson, or zero-inflated Poisson regression models, depending on the observed distributions of outcome behaviors. We also will explore analyzing substance use as time-to-event data using a Cox proportional hazards regression model with the SAS PHREG procedure with censoring if loss to follow-up occurs. Effect sizes will be computed from the model as differences between groups on adjusted means divided by SDs for the linear models, or differences between odds for logistic models or hazards for Poisson models.

The median and relevant percentile (e.g. 25th or 75th) of time to events will be presented by group with associated confidence intervals. All models will include an indicator variable for whether the subject was enrolled as a detained or probation youth. Other covariates will be included based on their theoretical importance as potential confounders and on their imbalance between randomized arms at baseline. We also will examine moderators that we have hypothesized to be potential determinants of treatment response (e.g., family functioning).

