##### Analyses

The specific analyses and hypothesis tests (which are preliminary because this is a feasibility study) will assess effectiveness of the brief intervention and ENCOMPASS on substance use outcomes. These data will be used to generate hypotheses about brief and comprehensive interventions for a future larger study.

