##### Sample size and power

We plan to recruit n = 80 youth and caregiver dyads per county (160 total). We estimate that no more than 10% of youth in each county will be high-risk, resulting in a sample size of n = 16 assigned to ENCOMPASS and n = 144 to first-stage brief intervention (BI). We anticipate 20% loss at 6-month follow-up resulting in n = 12 in the ENCOMPASS group and n = 116 in the first-stage BI with 6 month data (58 responders and 58 non-responders, assuming a 50% response rate. We have accounted for a sample size inflation factor related to potential within-county intraclass correlation (ICC) of outcomes. Specifically, in the first step of the back-calculation, we determined that a sample size of n = 40 per responders and non-responders to the first-stage intervention (with 6-month data) is required under the “independence of observations” assumption (i.e., *before* accounting for clustering) to provide 80% power for the two-sided model-based tests to detect an effect size (0.63) that is between medium (0.50) and large (≥ 0.80). For a first-stage effective sample size of 40 in each group (responder vs. non-responder), there is a 1.39 sample size inflation factor (IF) when the ICC = 0.01 and the number of clusters (i.e., counties) = 2: IF = [1 + (average 40 patients per cluster − 1) × ICC of 0.01]. Therefore, an actual sample size of 56 per first-stage brief intervention (i.e., 40 × 1.39) with 6-month data is required (i.e., an effective sample size of 40 per first-stage brief intervention with 6-month data if observations were not clustered). The sample of 56 in each group will provide adequate power for this feasibility study and its preliminary hypothesis tests, given that we anticipate n = 58 per first-stage group (responder vs. non-responder) with 6-month data. This power calculation is conservative because the longitudinal models will have slightly increased power due to incorporating all available data (baseline, 3-months, 6-months), including data from persons missing one but not all times points. The goal will be to estimate effect sizes, for which the planned sample size will be adequate. A minimum of 12 per group is recommended for estimating effects sizes of continuous outcomes in pilot or feasibility studies [44].

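### The powered effectiveness test compares responders with non-responders to the same brief intervention, a contrast that cannot show whether that intervention works

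*Protocol article*

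**What the plan says.** The abstract (Methods/design) states the aim: "We will measure the effectiveness of a brief and comprehensive intervention by assessing changes in substance use across treatment".

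Measuring treatment response forms the groups: "Those with a post-intervention score of 70% or higher will be considered “treatment responders", and lower scorers are non-responders. The cut-off is favoured partly because it gives "an anticipated equal sample-size split for responders and non-responders".

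Preliminary analyses sets the contrast, to "compare the primary treatment response outcome (confidence of abstaining measured by the BSCQ) and substance use outcome across the responders and non-responders", and names BSCQ as "the primary treatment response outcome (confidence of abstaining measured by the BSCQ". On the model it says "The baseline measure of BSCQ or substance use days will be adjusted as covariates", with the 3- and 6-month values as the repeated outcomes. Effect sizes are between-group differences in adjusted means divided by SDs. ENCOMPASS gets a separate model whose form is not given.

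The Analyses section says that the tests "will assess effectiveness of the brief intervention and ENCOMPASS on substance use outcomes", and calls them preliminary. Sample size and power then judges the sample adequate "given that we anticipate n = 58 per first-stage group (responder vs. non-responder) with 6-month data".

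**The concern.** Responder status is an outcome of treatment, not a treatment assignment. If both groups had the same brief intervention, the difference between them says who did well, not whether the intervention made anyone better. When the outcome is BSCQ again, the comparison asks whether youth with high scores after treatment still score higher later. Any stability of the measure within a person gives that result, even if the intervention does nothing.

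At stake is the trial's main clinical question. A significant responder difference, labelled as effectiveness and carried forward as an effect size for the larger study, could reflect within-person correlation alone. Whether use fell after treatment could go unreported.

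**Working it through.** **Which contrast is powered.** Inputs from Sample size and power: effect size 0.63, 80% power, two-sided; alpha is not stated and 0.05 is assumed.
- Two-sample formula: n per group = 2(1.960 + 0.842)² / 0.63² = 39.6, so 40.
- Inflation: 1 + (40 - 1) × 0.01 = 1.39, and 40 × 1.39 = 55.6, so 56.
- Available: 116 / 2 = 58 per group.

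The plan's 40 and 56 both reproduce. The arithmetic is sound, and it belongs to a two-sample comparison of responders with non-responders.

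**What that contrast shows when nothing works.** Assume standardised normal measures, no change in any mean, and a split at the median of post-intervention BSCQ (the plan expects about 50:50). The expected unadjusted gap is 2 × √(2/π) × r = 1.596r, where r is the correlation of post-intervention BSCQ with the later outcome. The planned effect of 0.63 SD therefore arises unadjusted at r = 0.63 / 1.596 = 0.39.

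With baseline as a covariate, the expected gap is

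0.399 × (ρ_py - ρ_pb × ρ_by) / (0.25 - 0.159 × ρ_pb²),

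where p is post-intervention BSCQ, b the baseline of the outcome and y the outcome at follow-up. Adjustment removes the gap only if ρ_py = ρ_pb × ρ_by, that is, if the post-intervention score carries no information beyond baseline.

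Simulation with n = 116, one follow-up and a nominal 5% test. All correlations are assumptions, because the document gives none.

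| Outcome | Correlations | Adjusted gap (SD) | Rejection with zero effect |
|---|---|---|---|
| BSCQ | all 0.2 | 0.26 | about 28% |
| BSCQ | all 0.3 | 0.36 | about 49% |
| BSCQ | all 0.5 | 0.47 | about 78% |
| Use days | with BSCQ 0 | 0 | about 5% |
| Use days | with BSCQ -0.2 | -0.16 | about 16% |
| Use days | with BSCQ -0.3 | -0.25 | about 33% |
| Use days | with BSCQ -0.4 | -0.36 | about 55% |

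For use days, own-baseline correlation is 0.5 and baseline use correlates with post-intervention BSCQ as strongly as later use does. The last row is sensitive to this: if the baseline correlation is -0.3 instead of -0.4, rejection is about 74%.

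Averaging the two BSCQ follow-ups, closer to the planned longitudinal model, gives 24–48% at 0.2 and 90–94% at 0.5 (range over AR(1) and exchangeable correlation). A within-person test of change from baseline to 6 months on the same null data rejects in 4–5.5%.

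**Later care.** Measuring treatment response sends non-responders to a second round of brief intervention; the Fig. 2 caption refers them to ENCOMPASS. On either account only one group receives further treatment, so the gap mixes prognosis with later care. Effective further treatment would narrow it.

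**Precision of the alternative.** The 95% CI half-width for mean change, in SDs of change, is t(n-1) / √n.
- n = 116: 1.981 / 10.77 = 0.18.
- If the protocol's ICC of 0.01 applies to change, with 58 per county: 0.184 × √(1 + 57 × 0.01) = 0.184 × 1.253 = 0.23.
- n = 12 (ENCOMPASS): 2.201 / 3.464 = 0.64.

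**The case against.** **Substance use days do not form the groups.** The Analyses section claims effectiveness on substance use, so circularity in the strict sense applies to BSCQ only. This stands. A reader might infer that a false-positive result is close to certain on every outcome. The document does not support that: for use days the inflation ranges from none to large, according to correlations that it does not give.

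**Baseline is not ignored.** Preliminary analyses lists baseline among the comparison times, and Sample size and power counts baseline among the data used. A covariate model can also yield average change, by setting adjusted follow-up means against the baseline mean. So it would be too strong to say that change from baseline cannot be obtained. What stands is that the described model uses baseline as a covariate and takes its effect size between responder groups, which does not match the abstract.

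**ENCOMPASS.** One might infer that its model has no usable estimand. The article does not give its form, and a condensed article may leave that to a fuller document. It is not a fault here.

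**One brief intervention or two.** A reader might take it as settled that every low- or mid-risk youth receives Teen Intervene. The abstract and Fig. 2 caption say so, but Risk level determination still randomises between Teen Intervene and Family Check-Up, and Preliminary analyses mentions randomised arms. The text does not settle this. Even with two arms, responder versus non-responder would not be the randomised comparison.

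**It is a feasibility study.** The tests are called preliminary and the stated goal is to estimate effect sizes. That lowers the stakes, but the plan still attaches effectiveness to these tests and powers this contrast. An effect size that can arise without benefit is a poor basis for a larger study.

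**Conclusion.** The point holds. The powered contrast does not answer the trial's question about the brief intervention, and better numbers would not change that. For BSCQ it is circular: zero-effect rejection is about 28–78% at correlations of 0.2 to 0.5 with one follow-up. For substance use days it is about 5–55% over correlations of 0 to -0.4. These sizes rest on assumed correlations, normality, a median split and alpha 0.05. That both groups received the same assigned treatment follows from the text only if there is one brief intervention. The mismatch with the abstract's aim of change across treatment, and the grouping by a post-treatment score, rest on the text alone.

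**What to change.** - Make within-person change the primary effectiveness analysis: baseline, month 3 and month 6 all as outcomes, visit as a factor, for all youth assigned to the brief intervention regardless of response. Use the same estimand in the separate ENCOMPASS model.
- Report mean change with 95% CI. Describe it as uncontrolled change under the whole assigned pathway, including any further treatment of non-responders; it does not isolate Teen Intervene.
- Keep responder versus non-responder as descriptive only.
- Replace the power statement for that contrast with the precision figures above: 0.18 SD (0.23 SD with clustering) and 0.64 SD.
- Reconcile Measuring treatment response with the Fig. 2 caption on what non-responders receive, and the remaining references to randomised brief interventions with the single-intervention description. If two brief interventions are in fact randomised, compare them as randomised instead.

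The cost is wording: the three assessments are already planned, and no extra participants or data are needed. The downside is a more modest claim, because without a control group change cannot be attributed to treatment.

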#### Community partner participants

Community partner participants will be clinicians, case managers, and supervisors working in the CMHC in each county (range n = 10–30). Bachelor’s level case managers from each CMHC site (n = 2 case managers for each county) will be recruited to act as intervention specialists. They will be trained in the brief intervention and provide treatment to YIJJ and their caregivers. Master’s level licensed clinicians from each CMHC (n = 2 for each county) will be trained in the comprehensive substance use intervention and provide treatment to YIJJ.

The juvenile justice system in each county have agreed to participate and implement substance use screening. Designated juvenile probation officers/intake officers will be identified and will be responsible for conducting universal substance use screening with all youth coming through the detention center at intake.

In addition to these primary individuals who will provide interventions, we will seek participation from other personnel (e.g., juvenile justice intake staff, CMHC supervisors) who are involved in the implementation and sustainability of the interventions to complete qualitative interviews and quantitative measures to assess feasibility and implementation in these settings.

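### The sample size allows for correlation of outcomes within county, but the youth-level models commit to no county term

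*Protocol article*

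**What the plan says.** Sample size and power (protocol article) treats county as a source of correlation: "We have accounted for a sample size inflation factor related to potential within-county intraclass correlation (ICC) of outcomes". It gives the size of the allowance: "there is a 1.39 sample size inflation factor (IF) when the ICC = 0.01 and the number of clusters (i.e., counties) = 2". The calculation is for "two-sided model-based tests" of responders against non-responders to the first-stage brief intervention.

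Preliminary analyses describes those models as longitudinal generalized linear models. The baseline value of the outcome is a covariate, and the 3- and 6-month values are analysed together. One further term is fixed for every model: "All models will include an indicator variable for whether the subject was enrolled as a detained or probation youth". Other covariates may be added on theoretical grounds as possible confounders and according to baseline imbalance between randomized arms. County does not appear as a covariate, a fixed or random effect, or a level of clustering. Neither does the person who delivers the intervention.

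On delivery, Community partner participants says "n = 2 case managers for each county) will be recruited to act as intervention specialists", so four people give the brief intervention across the two counties. Study setting says that each county has one primary community mental health center, so county and treatment site coincide.

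**The concern.** The plan recruits extra youth because it expects outcomes to be alike within a county, but the analysis it describes does not commit to using county. A larger sample does not take a difference between counties out of an estimate. Only the model or a stratified presentation can do that.

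Responder status is decided after treatment, by a mean score of at least 70% on the confidence questionnaire (BSCQ). A county with better resources or staff could have more responders and also better outcomes at 3 and 6 months. Responders would then come disproportionately from that county, and the contrast would carry part of the county difference. In the opposite pattern the contrast would shrink. The stated goal is to estimate effect sizes, and the data are meant to inform a larger study, so a reader would want to know whether a result comes from one county.

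**Working it through.** **The plan's own figures.** The inputs are in Sample size and power: "80% power for the two-sided model-based tests to detect an effect size (0.63" SD. Alpha is not stated; 0.05 two-sided is assumed.

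- n per group = 2 × ((1.960 + 0.842) / 0.63)² = 39.55, rounded up to 40. This agrees with "a sample size of n = 40 per responders and non-responders to the first-stage intervention (with 6-month data) is required".
- The inflation factor is given as "IF = [1 + (average 40 patients per cluster − 1) × ICC of 0.01": 1 + 39 × 0.01 = 1.39.
- 40 × 1.39 = 55.6, rounded up to 56.

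The stated 40, 1.39 and 56 all reproduce, so the design stage does allow for county.

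**What the contrast absorbs without a county term.** Assume equal numbers in the two counties (the plan recruits 80 in each). Let pA and pB be the response rates.

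- Share of responders from county A = pA / (pA + pB).
- Share of non-responders from county A = (1 − pA) / (2 − pA − pB).
- Amount absorbed = (difference of these shares) × (difference between county means).

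For the county difference, take one standard deviation of the difference between two county effects, √(2 × ICC), in SD units of the outcome. At the plan's ICC this is √0.02 = 0.141.

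- Rates 50% and 50%: shares 0.5 and 0.5, difference 0, amount 0.
- Rates 60% and 40%: shares 0.6 and 0.4, difference 0.2, amount 0.2 × 0.141 = 0.028 SD.
- Rates 70% and 30%: shares 0.7 and 0.3, difference 0.4, amount 0.4 × 0.141 = 0.057 SD.

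Relative to 0.63, the last two are 4% and 9%. The response rates by county are assumptions; the protocol gives only an overall 50%. The ICCs of 0.05 and 0.10 below are also assumptions, to show the range.

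| ICC | √(2 × ICC) | 50% / 50% | 60% / 40% | 70% / 30% |
|---|---|---|---|---|
| 0.01 (plan) | 0.141 | 0 | 0.028 | 0.057 |
| 0.05 | 0.316 | 0 | 0.063 | 0.126 |
| 0.10 | 0.447 | 0 | 0.089 | 0.179 |

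**The same mechanism at provider level.** The protocol gives no provider ICC. With equal caseloads, the 116 brief-intervention youth with 6-month data are 116 / 4 = 29 per case manager. Trials with no true group difference were simulated, 5,000 per setting, with provider effects drawn at random.

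- With equal response rates, the rejection rate without provider terms was 0.044, 0.052 and 0.056 at ICC 0.01, 0.05 and 0.10. It was nearly the same with them (0.044, 0.054 and 0.056).
- With response rates running from 30% to 70% across providers, it was 0.054, 0.067 and 0.082 without provider terms, and 0.049 to 0.050 with them.

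The simulation error is about 0.003, so the excess at ICC 0.01 is barely distinguishable from none.

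**The case against.** The strongest reply is that the covariate list is not closed. A county effect is a natural candidate on theoretical grounds, and an article may leave the full list to an analysis plan that is not shown. This stands in part: the text does not exclude county. But the article chose to say what every model contains, and it assumed county correlation for those same tests, so the two sections should agree. The open clause commits to nothing on county. It also leans partly on imbalance between randomized arms, whereas responders and non-responders are not randomized arms.

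The second reply is that the effect is small and conditional. This stands. Both groups occur in both counties, so nothing is absorbed unless response rates differ. At the plan's ICC the amount is small, and the section headed Analyses calls the tests preliminary because this is a feasibility study.

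Three stronger readings are tempting, and the documents do not support them.

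- A reader might infer that omitting county and provider necessarily biases the contrast. It does so only if response rates and outcomes both differ across sites or providers, and nothing in the protocol shows that they will.
- A reader might infer that, with only four case managers, intervals for an overall brief-intervention mean are far too narrow. No provider ICC is given, and Preliminary analyses describes comparisons between groups, not a model for an overall mean. The understatement arises only when generalising beyond these four people, and fixed effects would not cure it.
- A reader might infer that a four-level provider factor belongs in the main model. Limitations says that case-manager turnover is high. Non-responders go on to a second round of brief intervention or, according to the Fig. 2 legend, to ENCOMPASS, which other staff deliver. Some youth may therefore have no single provider.

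**Conclusion.** The mismatch holds for county. The sample size is inflated by 1.39 for within-county correlation, yet the models commit only to baseline outcome and detained or probation status, so no committed term accounts for county. The consequence is modest: about 0.03 to 0.06 SD in the responder versus non-responder contrast. That rests on the plan's ICC of 0.01, a county difference of one standard deviation, equal county sizes, and assumed response rates of 60% versus 40% to 70% versus 30%. It is zero if response rates are equal. At an assumed ICC of 0.10 it would be 0.09 to 0.18 SD, but nothing in the protocol supports a value that high.

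This is an inexpensive improvement, not a flaw that undermines the study. Nor does adjustment change what the contrast is: responder status is defined by the post-treatment confidence score, which is also an outcome, so the comparison is not a treatment effect with or without a county term.

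**What to change.** In Preliminary analyses, name county as a fixed effect in all youth-level effectiveness models, including the separate ENCOMPASS model. Show results by county, and state that inference is to these two counties. A random county effect or cluster-robust standard errors are not workable with two clusters.

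As a sensitivity analysis, adjust for the first-stage brief-intervention provider or give descriptive results by that provider. Say how youth without a single provider are handled.

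The cost is one or two sentences and 1 degree of freedom per model, out of about 116 youth in the brief-intervention models and about 12 in ENCOMPASS, where it is felt more. County is already known for every youth, so no new data are needed, and the sample size need not change on this account.
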